A practice block of 16 trials will be completed (using 8 neutral emotional stimuli, involving each of the cued locations, and neutral cues).In each trial, participants fixate on a word (“Ready”) at the centre of the screen for 500 ms prior to cue onset (Fig. 2).The cue (a seated male figure) will be presented for 2000 ms in the middle of the screen, either with one of three locations highlighted at random using a red, highly luminous highlighted rectangular area (see [68, 79]), or no location highlighted. The three locations will be the chest, lower abdomen, or shins (pressed together in the image to form a single area). All highlighted areas will be the same size, colour, and luminescence. The image will be large (345 × 715 pixels), and the highlighted area as luminescent as possible within the limitations of the package used to create it (*Microsoft Office Word, version* 16.23).The emotional stimuli (selected IAPS and NAPS images; see Additional file 2) will be either 600 × 800 pixels or 800 × 600 (i.e. landscape or portrait), all at a resolution of 72 pixels/inch. The stimuli will be delivered at an inter-stimulus interval (ISI) of 200 ms, remaining for 200 ms (changes in levels of arousal do not increase significantly beyond 150 ms presentation duration [61]). With picture stimuli being presented to elicit exogenous attention, a mixture of neutral and negative emotional images will be presented to control for the effect of sudden onset of a stimulus. Further, since negative stimuli tend to reliably create the highest level of physiological arousal in men and women, this will be important for creating detectable changes in the body. Again, to ensure that the cues do not become task-relevant (i.e. predictive of a target stimulus and hence endogenous), the frequency of valid cues will be kept to below 70% of trials. Although it is not known in advance what a “valid” cue is in this bespoke variant of the spatial cueing task, for the purposes of setting up the cues these are limited to the chest and lower abdomen areas (interoceptive/visceroceptive areas), each with 31% of “valid” cues, which remains within the standard limits (i.e. 62% in total). A further 10% of trials will be “invalid”, i.e. the shins (a non-interoceptive/visceroceptive area).In 15% of trials, there will be no emotional stimulus following a cue (catch trials); plus, in a further 14% of trials, there will be a neutral cue (no cue areas highlighted)^2^.Non-catch “valid”, “invalid”, and neutral trials will be further split into calculated proportions of negative and emotionally neutral target stimuli. In total, there will be 65% negative and 20% neutral stimuli (along with the 15% catch trials).Participants are required to give a speeded response: a mouse click upon detection of a bodily change—anywhere in the body—but they will be instructed to be sure of detection (i.e. guesses are discouraged; see [77]). It is important to separate this initial response from the indication of a location in order to clearly disambiguate (i) no emotional feeling being detected and (ii) an emotional feeling being detected but when the location was not known. If no response is registered within 6000 ms, the next trial is presented.If a change was detected, then participants transition to another screen to indicate a location on a virtual body by mouse click, followed by an indication of the valence and intensity of the detected feeling (using the *Self-Assessment Manikin*; for a similar approach, see [19]). If a location was detected but it was not known where, this can be indicated by clicking outside of the body area. The time taken to give these further responses will assist with a likely longer refractory period for an embodied emotional response compared with, say, visual attendance. (See, for instance [80], where the mean cardiovascular recovery time following an emotional film stimulus—lasting up to 100 s in duration—was approximately 30 s. The estimated time per trial in the current spatial cueing task, including an inter-trial interval of 200 ms, is around 15 s, but where a picture stimulus will be presented and for a far shorter duration of 200 ms, which may then result in a shorter recovery period than a relatively lengthy film.) This process will be repeated throughout all blocks, where the cued response is exogenous.In total, there will be 6 main blocks, with a brief rest period between them, and 248 trials. Based on the percentages stated previously, this will result in 152 valid trials (76 lower abdomen; 76 chest), 26 invalid trials (shins), 37 catch trials, and 34 neutral cue trials (where no part of the body is highlighted). For each of the valid sets of trials, 58 emotional stimuli will be negative and 18 will be neutral. For invalid trials, 20 will be negative and 6 will be neutral. For neutral cue trials, 26 images will be negative and 8 will be neutral. For catch trials (no emotional stimulus), there will be 10 sets of each of the 3 bodily locations, with one set of 7 neutral locations (no areas cued on the image of a seated person).Finally, to control for order effects, blocks will be counterbalanced: one half of each of the groups (assigned at random) will complete blocks in the order 1–6. The other half will complete the blocks in reverse order.

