### Dependent variables (spatial cueing task only)

Frequency of response to emotional stimuli;Intensity of experience (continuous);Valence reported ([positive] vs. [negative] vs. [neutral]);Location of felt experience (point indicated on a human model; to be coded into a categorical measure).

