### Spatial cueing task

One of the interoception groups will show significantly faster reaction times (RTs) and greater response frequency to emotional stimuli regardless of cue type compared with each of the other groups after baseline; plus, there will be a greater change between baseline and follow-up. Each of the interoception groups separately and combined will show significant differences from the control group.One set of cues for the same group (i.e. the interoception group in (1)) will facilitate significantly faster RTs and greater response frequency. This set will match the target area of the body for that group (i.e. a chest cue for the cardioception group; a lower abdomen cue for the gastroception group). The “matching” cue for the other interoception group will not facilitate faster RTs or greater response frequency. If any cue facilitates faster RTs or greater response frequency for the other groups, it will be the same cue that facilitates for the interoception group in (1).This same group will display greater within-group coherence in the location of the body indicated to be active during trials compared with the other groups after baseline. It will also show the greatest change between baseline and follow-up compared with the other groups.This same group will report greater intensity compared with the other groups after baseline. It will also show the greatest change between baseline and follow-up compared with the other groups. The interoception groups combined will report greater intensity than the control group.This same group will show greater heart rate deceleration after baseline following the presentation of emotional stimuli compared with the other groups; both interoceptive groups will show greater heart rate deceleration than the control group.

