## Data analysis

Generalised Estimating Equations (GEE) will be used to analyse the two data points, including variable interactions. GEE can account for repeated measures as well as the potential problem that the primary outcome variable (RT) may not be normally distributed (although it will be continuous). Using GEE, the effects of the predictors on RT can be modelled under different circumstances, and the interrelationships between predictors can also be investigated. Significance testing will be undertaken at the *p* < 0.05 level.

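### Hypothesis 4 compares felt intensity only on trials that were clicked, while hypothesis 1 expects training to change which trials are clicked, so the contrast is biased by an unknown amount

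*Protocol article*

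**What the plan says.** In the protocol article, under Hypotheses, Spatial cueing task, the first hypothesis reads: "One of the interoception groups will show significantly faster reaction times (RTs) and greater response frequency to emotional stimuli". The fourth concerns that group again: "This same group will report greater intensity compared with the other groups after baseline". It also predicts the largest change from baseline in that group, and higher intensity in the two trained groups combined than in controls.

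The procedure under Data collection procedures, Spatial cueing task, fixes when a rating exists. Of the speeded click, it says that participants may respond to a change anywhere in the body but "they will be instructed to be sure of detection". After a click: "If a change was detected, then participants transition to another screen to indicate a location on a virtual body by mouse click". Once the location is marked, the procedure adds the rating itself: "followed by an indication of the valence and intensity of the detected feeling". Without a click: "If no response is registered within 6000 ms, the next trial is presented". No intensity is taken on such a trial.

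Under Variables, response frequency and intensity are separate dependent variables of this task. Intensity is listed as continuous, and no value is given for a trial without a click. Data analysis says: "Generalised Estimating Equations (GEE) will be used to analyse the two data points, including variable interactions". Neither that section nor Limitations mentions that the rated trials are a selected subset. The article gives no expected click rate, intensity SD or intensity effect.

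**The concern.** Randomisation makes the groups comparable on the full set of picture trials. It does not make them comparable on the subset each participant chooses to click, because that choice comes after randomisation and is itself expected to respond to training. Suppose training lets people notice fainter sensations. The Background suggests something close to this when it proposes that sustained practice gradually lifts inhibition of bodily awareness. The added clicks would then tend to come from weaker sensations and pull the mean rating down, although nothing is felt less strongly. Success on hypothesis 1 would then work against hypothesis 4. Conversely, a group that clicks only on its strongest sensations could seem to feel more intensely.

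Unweighted GEE does not remove this, because whether a rating is missing depends on the value that would have been given. At stake is the interpretation of hypothesis 4: a null or reversed result could not be told apart from improved detection, and a positive result could misstate the size of the rise.

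**Working it through.** **The plan's own figures.** The article has no figure for intensity or click rate to reproduce. Its sample size of 54 concerns reaction time and does not bear on this point. Picture trials per visit, from the trial counts in the procedure: 2 × 76 + 26 + 34 = 212. Check by picture type: negative 2 × 58 + 20 + 26 = 162; neutral 2 × 18 + 6 + 8 = 50; 162 + 50 = 212.

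**Model (assumed).** Each picture trial has a latent intensity X, normal with mean μ and SD 1. The participant clicks, and so gives a rating, only when X exceeds a threshold c. Then

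- click rate = 1 − Φ(c − μ)
- mean rated intensity = μ + φ(c − μ) / [1 − Φ(c − μ)]

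At baseline μ = 0, and c is set by the assumed click rate.

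**Worked case, baseline click rate 50% (c = 0).**

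- Baseline mean: φ(0)/0.5 = 0.3989/0.5 = 0.798.
- Threshold drop of 0.5, no true change (μ = 0, c = −0.5): click rate 0.6915; mean 0.3521/0.6915 = 0.509. Change 0.509 − 0.798 = −0.289.
- True rise of 0.5, fixed threshold (μ = 0.5, c = 0): click rate again 0.6915; mean 0.5 + 0.509 = 1.009. Change +0.211, or 0.211/0.5 = 42% of the true rise.
- Both (μ = 0.5, c = −0.5): mean 0.5 + 0.288 = 0.788. Change −0.010, or −2% of the true rise.

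The first two scenarios give the same click rate after training (69%), so the click rate alone cannot separate them.

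**Over the range of baseline click rates.**

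| Baseline click rate | Threshold drop only: change (SD) | True rise only: share shown | Both: share shown |
|---|---|---|---|
| 10% | −0.40 | 20% | −54% |
| 30% | −0.35 | 31% | −27% |
| 50% | −0.29 | 42% | −2% |
| 70% | −0.22 | 56% | 27% |
| 80% | −0.17 | 66% | 45% |
| 90% | −0.11 | 78% | 67% |

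With a fixed threshold, more than half of the rise is hidden only below a baseline click rate of about 62% (67% if the true rise is 0.2 SD).

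**Sensitivity to the model.**

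- Exponential intensity, fixed threshold: 100% of the rise is shown. A pure threshold drop still lowers the mean.
- Lognormal intensity with a 30% gain, fixed threshold: 50% to 89% is shown. A pure threshold drop again lowers the mean.
- Normal model at a 50% click rate, with detection strength correlated only 0.5 with intensity: 71% is shown with a fixed threshold, since 0.5 + 0.5 × (0.509 − 0.798) = 0.356 and 0.356/0.5 = 71%. With the threshold drop added, 49% is shown. At correlation 0 nothing is hidden.

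**Scoring trials without a click.** As an illustration, score them 0 on an assumed scale with mean 5 and SD 2, over baseline click rates of 30% to 90%. The all-trials mean rises by 0.13 to 1.05 points for the threshold drop alone, 1.09 to 1.56 for the true rise alone, and 1.14 to 2.61 for both. The sign reversal disappears, but the score also rises when only detection improves.

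**The case against.** The strongest reply has four parts.

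First, a reader might infer that training must lower measured intensity and that most of a real rise will be hidden. The documents do not support that. They give no click rate. Most trials carry negative pictures and the task seeks high arousal, so a high rate is as plausible as a low one. At 80% to 90% with a fixed threshold, 66% to 78% of a rise remains visible, and even with the threshold drop the net change is positive. This stands, and it limits the claim about size and direction.

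Second, clicking and rating are separate responses. Extra clicks might come from attention to the trained area or from faster detection within the time limit, and the article's premise is that better visceroception goes with greater intensity. Newly detected feelings need not be the weakest. This also stands: the loss depends on a link between detection and rating that the article does not establish.

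Third, the article does not say how intensity will be summarised, and an analysis plan not shown may define a score for trials without a click. That is fair as to scoring. It does not remove the selection, because no plan can recover ratings that were never taken.

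Fourth, frequency and intensity are already separate outcomes, intensity is secondary to reaction time, and in the predicted direction the bias works against the hypothesis. That makes the matter less serious. But listing both outcomes does not stop conditional intensity from being read as a randomised comparison, which is how hypothesis 4 is worded.

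**Conclusion.** The point holds in a limited form. Hypothesis 4 rests on ratings that exist only after a click, and hypothesis 1 predicts that training alters clicking in the same group, so the intensity contrast is conditioned on a post-randomisation outcome. That follows from the article's own text. The size of the bias, and possibly its direction, do not.

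Under the normal model with one scale for clicking and rating, and assumed baseline click rates of 10% to 90%, a pure 0.5 SD threshold drop looks like a loss of 0.40 to 0.11 SD, and a true 0.5 SD rise with a fixed threshold shows as 20% to 78% of its size. When both occur, the net change can be negative, near zero or positive. Other latent distributions, or a weak link between detection and rating, hide less or nothing. The change should be made, because it alters what can be concluded on hypothesis 4. It does not touch the primary reaction-time outcome.

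**What to change.** - State that intensity given a click is conditional on response and is not by itself a randomised comparison.
- Add a comparison over all 212 picture trials per visit, scoring a trial without a click as no change felt, below the lowest rating, with an ordinal model as a check on that scoring.
- Report this comparison together with its two parts, the click rate and intensity given a click, by group and visit.
- Claim neither greater nor lesser intensity from intensity given a click alone, nor from the all-trials score alone when a higher click rate could explain it.

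This needs analysis wording and no new data. The cost is in interpretation. The all-trials score mixes frequency with strength, and used alone it would let hypothesis 4 succeed through more clicking. It therefore supplements the conditional measure and does not replace it, and the conclusion on hypothesis 4 becomes more guarded.

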### Stop/signal task

6.This same group will show significantly slower RTs on the stop-signal task after baseline and a greater change in RTs between baseline and follow-up compared with the other groups, but with each of the interoceptive groups separately and combined showing significantly slower RTs compared with the control group.

### Hypotheses on interoception and emotion regulation:

7.Both interoceptive groups will show increases in interoceptive sensitivity (measured by the Schandry task and water load test), sensibility (measured by the MAIA), and metacognitive awareness over the study period, but there will be no significant differences between each other either at baseline or between baseline and follow-up. They will each be significantly different from the control group on these measures. Further, the cardioception group will show the greatest improvement on the Schandry task, and the gastroception group will show the greatest improvement on the water load test.8.The two experimental groups will each show significant improvements over the control group on the *DERS*, the *ERS*, and the *SF-36* (emotional well-being sub-scale) scores between baseline and follow-up, with the same group as in (1) showing greater improvements compared with both of the other groups.

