### Sample size

A power analysis calculation was based on reaction time (RT) measures in Silverstein et al. [34], who reported a mean RT of 2134.1 ms (SD = 856.6 ms) pre-treatment and 1403.6 ms (SD = 462.3 ms) post-treatment for meditators, and 1865.1 ms (SD = 800.4 ms) pre-treatment and 1893 ms (SD = 780.6 ms) post-treatment for controls. This gave a treatment-by-time partial eta-squared of 0.15, with a *p* value of 0.03. Using the same partial eta-squared for the three group, two time point studies, with alpha = 0.05 and 80% power, a minimum of 54 participants would be required in total (across all group conditions). This equates to a minimum of 18 participants per group to detect the main effect in the spatial cueing task. (regarding the stop/signal task, Verbruggen and De Houwer [35] detected effects in a single group with a sample size of 23 participants.) We will aim for 70 participants in total, assuming a drop-out buffer of approximately 5–10 participants. This will allow 20+ participants in each group.

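### Hypothesis 7 predicts both no difference and a difference between the two interoception groups on the same two tests, and makes non-significance its evidence of similarity

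*Protocol article*

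**What the plan says.** **Hypothesis 7** (Hypotheses on interoception and emotion regulation) covers sensitivity, sensibility and metacognitive awareness, and identifies sensitivity with the Schandry task and the water load test. Both interoception groups are to improve, but "there will be no significant differences between each other either at baseline or between baseline and follow-up". The paragraph ends by predicting that cardioception gains most on the Schandry task and that "the gastroception group will show the greatest improvement on the water load test".

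**Hypothesis 2** (Hypotheses, Spatial cueing task) predicts that the matching cue speeds responses significantly in whichever interoception group leads under hypothesis 1, and that the matching "cue for the other interoception group will not facilitate faster RTs or greater response frequency".

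**Data analysis** gives GEE with interactions and a 0.05 significance level. **Design** plans a gastroception versus cardioception comparison, while the predictor list under **Variables** describes group only as interoception groups against control.

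**Sample size** is set for one effect: "This equates to a minimum of 18 participants per group to detect the main effect in the spatial cueing task". The target is stated as "We will aim for 70 participants in total", and after drop-out "This will allow 20+ participants in each group".

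**The concern.** Two things in hypothesis 7 look wrong as written. The same two groups are predicted not to differ, and to differ, in change on the same two tests. A given result on either test can then satisfy one sentence and contradict the other. Separately, the predicted outcome is the absence of significance, which a small trial produces easily whether or not the groups are alike.

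Hypothesis 2 raises a related risk. It pairs a significant effect in one group with no effect in the other and does not state the contrast that compares them. Research questions 1 and 2, on whether emotion is localised and whether training reveals it, depend on this. If the analyst judged each group separately, chance could split two groups that respond identically.

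**Working it through.** **1. The plan's own figure.** The article gives "This gave a treatment-by-time partial eta-squared of 0.15", and "with alpha = 0.05 and 80% power, a minimum of 54 participants would be required in total". f² = 0.15/0.85 = 0.1765. A large-sample 2-df test with 80% power needs noncentrality 9.635, so N = 9.635/0.1765 = 54.6. This agrees with the stated 54 to within rounding. The noncentral F version needs 58. Either way the number is sized for the three-group effect on reaction time, not for a two-group comparison on the interoception measures.

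**2. Group sizes.** Minimum 18 per group; 70/3 ≈ 23 before drop-out; 60 to 65 after losing 5 to 10, so 20 to 21 per group. I use 18, 20 and 23.

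**3. The two sentences of hypothesis 7 side by side.**
- Sentence one: groups, cardioception and gastroception; quantity, change from baseline; measures include the Schandry task and water load test; prediction, no significant difference.
- Last sentence: same groups, same quantity, same two tests; prediction, each group is best on its own test.

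They can be reconciled in two ways. One is that sentence one refers to a composite, which is not defined; the section on measuring interoception speaks of two methods. The other is that greatest means only numerically greatest, which is not a testable hypothesis.

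**4. What non-significance is worth.** Two-sided two-sample t-test, alpha 0.05, differences in SD units of the change score. Half-width = t(0.975, 2n−2) × √(2/n).

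| n per group | t × √(2/n) | 95% CI half-width | P(non-significant), true 0.5 SD | P(non-significant), true 0.8 SD |
|---|---|---|---|---|
| 18 | 2.032 × 0.333 | 0.68 | 0.69 | 0.355 |
| 20 | 2.024 × 0.316 | 0.64 | 0.66 | 0.31 |
| 23 | 2.015 × 0.295 | 0.59 | 0.62 | 0.24 |

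The difference detectable with 80% power is 0.96, 0.91 and 0.85 SD respectively. The article gives no SDs for these measures, so 0.5 and 0.8 SD are assumed values.

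**5. Could similarity be shown instead?** Two one-sided tests at 0.05, true difference zero, 20 per group: power is 3% for a margin of 0.5 SD, 60% for 0.8 SD and 86% for 1.0 SD. The margins are assumptions.

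**6. Hypothesis 2, if each group were judged separately.** Let p be the power of a one-sample test with n = 20. With identical true effects, exactly one group is significant with probability 2p(1−p).
- 0.3 SD: p = 0.247, giving 0.37
- 0.45 SD: p = 0.480, giving 0.50
- 0.6 SD: p = 0.721, giving 0.40
- Outside that range: 0.10 at 0 SD, 0.14 at 0.8 SD, 0.02 at 1.0 SD

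A direct comparison of the two groups' own-cue effects errs in 5%.

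**7. Coding of the cue.** The Variables section codes cue by body area. Suppose both groups gain the same amount d from their own cue. Chest minus abdomen is then +d in one group and −d in the other, so the group-by-cue-by-time interaction is 2d, not zero. With 20 per group and SD 1 for that contrast, it is significant in 46%, 79% and 96% of trials at d = 0.3, 0.45 and 0.6. An interaction in that coding would not separate one-area localisation from equal gains in both groups.

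**The case against.** **Hypothesis 7.** The variable list treats sensitivity as one continuous measure, and the closing sentence can be read as a refinement: equal overall gain with opposite task profiles. That is coherent, so the two sentences are not a strict logical impossibility. It needs a composite, however, and the article defines none. The case for reconciling the wording stands.

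**Hypothesis 2.** A reader might infer that the article tests localisation by an invalid rule, counting one group significant and the other not, and that it would wrongly declare localisation in 37% to 50% of trials. The document does not support this. The wording says the cue will not facilitate and does not mention significance. The analysis section allows interactions, and the design section plans the direct comparison. The rates also count a split in either direction, use one outcome where the hypothesis names two, and assume effects where such splits are most frequent. If which group leads under hypothesis 1 is unrelated to chance in the cue effect, they halve to about 19%, 25% and 20%, before requiring that hypothesis 1 succeed at all.

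**Equivalence margin.** A margin may be set in an analysis plan that is not shown, so its absence alone is no fault. The stated prediction of non-significance is.

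**Conclusion.** The point holds for hypothesis 7. Its statements about the Schandry task and water load test conflict unless an undefined composite is intended. Its similarity prediction would be met in roughly two trials out of three (62% to 69%) if the groups truly differed by 0.5 SD, so meeting it is not evidence of similarity. The baseline part of the prediction is uninformative, because any baseline difference between randomised groups is due to chance. These figures assume simple two-sample comparisons of change, two-sided at 0.05, with 18 to 23 per group.

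For hypothesis 2 the conclusion is limited: the contrast that carries the localisation claim should be named. The split rates illustrate the risk for the cue component alone, under assumed effects of 0.3 to 0.6 SD. They are not an error rate of the plan.

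**What to change.** 1. **Split hypothesis 7 by measure.** For the Schandry task and water load test, remove the clause predicting no significant difference. Test specificity as a group-by-task interaction, cardioception versus gastroception, on standardised change with both tests scored so that higher means better.
2. **Sensibility and metacognitive awareness.** Report the between-group difference with its 95% confidence interval and do not claim similarity from p > 0.05. At this sample size an equivalence claim is feasible only for a margin of about 1 SD.
3. **Baseline.** Drop the significance prediction.
4. **Hypothesis 2.** State that the claim rests on a direct contrast: the change in each group's own matching-cue effect (matched cue minus the shin or neutral cue), compared between cardioception and gastroception, with cue recoded as matched or unmatched. State the coding explicitly, for the reason in step 7 of the working. This contrast also contains any general chest-versus-abdomen cue effect, so the control group's chest-minus-abdomen change should be shown beside it.

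The cost is wording in the hypotheses and analysis sections, with no new data. The downside is that the between-group contrast has less power than separate within-group tests, so a true localisation effect may go undetected at about 20 per group.

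### Hypothesis 7 predicts no significant difference between the two trained groups on the heartbeat and water load tests, and also predicts that each group improves most on its own test

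*Protocol article*

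**What the plan says.** Hypothesis 7 stands in the protocol article under Hypotheses on interoception and emotion regulation. It opens: "Both interoceptive groups will show increases in interoceptive sensitivity (measured by the Schandry task and water load test", and goes on to sensibility (the MAIA) and metacognitive awareness. For the comparison of the two trained groups it predicts that "there will be no significant differences between each other either at baseline or between baseline and follow-up". Each trained group is then expected to differ significantly from control on the same measures. The closing sentence adds that "the cardioception group will show the greatest improvement on the Schandry task" and that "the gastroception group will show the greatest improvement on the water load test".

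The only decision rule given is in Data analysis: "Significance testing will be undertaken at the *p* < 0.05 level". Under Sample size, the trial is sized on reaction time in the spatial cueing task, with at least 18 per group needed and 20 or more expected. No SD, effect size or margin is given for the heartbeat task, the water load test, the MAIA or metacognitive awareness.

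**The concern.** The no-difference prediction and the greatest-improvement predictions cover the same two groups, the same two tests and the same change from baseline to follow-up. With three groups, improving most includes improving more than the other trained group. A result can therefore be reported as support under one sentence and as refutation under the other.

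There is a second problem even without that clash. The predicted similarity is worded as absence of significance, and the trial was not sized for this comparison. Small groups make such a prediction easy to meet whether or not the training effects differ. The baseline part carries no information about training, because under random allocation any baseline difference is a chance one.

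What is at stake is the reading of a secondary hypothesis: whether heart-focused and gut-focused training produce different or similar gains in interoception.

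**Working it through.** **1. The two predictions side by side**

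| Measure | First part of hypothesis 7 | Last sentence of hypothesis 7 |
|---|---|---|
| Schandry task, change | trained groups do not differ significantly | cardioception improves most |
| Water load test, change | trained groups do not differ significantly | gastroception improves most |
| MAIA, change | trained groups do not differ significantly | nothing |
| Metacognitive awareness, change | trained groups do not differ significantly | nothing |

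The clash is confined to the first two rows.

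**2. The plan's own sample size.** The plan states "This gave a treatment-by-time partial eta-squared of 0.15" and "with alpha = 0.05 and 80% power, a minimum of 54 participants would be required in total". Then f² = 0.15/0.85 = 0.1765. A 2-df chi-square test needs noncentrality 9.635 for 80% power, so N = 9.635/0.1765 = 54.6, which agrees with 54 to within rounding. (A noncentral-F version with N − 3 error df gives 58.) The figure concerns reaction time, so it says nothing about the tests in hypothesis 7. It matters here only because it fixes the group size.

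**3. Group size.** 70 recruited less 5 to 10 lost leaves 60 to 65, or 20 to 21.7 per group. I use 20, with 18 (the stated minimum) and 23 (70/3 rounded down) as the range.

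**4. How often a real difference is non-significant.** Assumptions: two-sided 0.05 (sidedness is not stated), a two-sample t-test on change, and true differences d in SD units chosen for illustration.

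- df = 2 × 20 − 2 = 38; critical value c = 2.024; noncentrality δ = d × √(20/2) = 3.162d.
- P(non-significant) = F(c; 38, δ) − F(−c; 38, δ), with F the noncentral t distribution function.
- For both tests, treated as independent, square it.

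| True difference d | δ | One test non-significant | Both tests non-significant |
|---|---|---|---|
| 0.2 SD | 0.632 | 91% | 82% |
| 0.5 SD | 1.581 | 66% | 44% |
| 0.8 SD | 2.530 | 31% | 9% |

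At 0.5 SD the pair is 69% and 48% with 18 per group, and 62% and 38% with 23. The 95% confidence interval for the difference at 20 per group has half-width 2.024 × √(2/20) = 0.64 SD, so a non-significant result is compatible with differences larger than 0.5 SD.

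**5. If greatest means only the largest point estimate.** Suppose the trained groups are truly equal and both clearly beat control. Each test then puts the predicted group first with probability 0.5, and both do so with probability 0.5 × 0.5 = 25% if the tests are independent. Requiring non-significance on both as well gives 0.475 × 0.475 = 23%.

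**6. How the two parts pull apart.** With a true own-test advantage of 0.8 SD on each test, non-significance on both holds 9% of the time. With no advantage it holds 0.95 × 0.95 = 90% of the time, but the ranking then rests on chance.

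**The case against.** The best defence is that the last sentence of hypothesis 7 does not use the word significant, whereas hypotheses 1, 2, 6 and 8 and the middle of hypothesis 7 do. A numerical ranking can coexist with non-significant pairwise differences, so this is not a strict logical contradiction. That stands, but the price is that the own-test prediction is then not tested at all.

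A second defence is that the predictor list under Variables treats interoceptive accuracy/sensitivity as one continuous measure, so the first sentence might concern an overall construct. No rule for combining the two tests is given, and hypothesis 7 itself defines sensitivity by both tests and then refers to these measures in the plural. The reading is possible but unsupported.

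Third, the difference sizes used above are assumptions. The only design effect, partial eta-squared 0.15, corresponds to d = 2 × √0.1765 = 0.84 for two groups. At that size non-significance occurs about 26% of the time on one test and 7% on both. It is a reaction-time effect against untrained controls, so it is only indicative for a comparison of two trained groups, but it shows why a range is needed.

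Several stronger readings are tempting and are not supported:

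- A reader might infer that the protocol formally scores a non-significant result as proof of similarity. It does not say so. It gives an alpha level and words the prediction as non-significance, and an analysis plan that is not shown could add a margin. Such a plan would not remove the clash within the hypothesis.
- A reader might infer the same flaw in hypothesis 2, where the matching "cue for the other interoception group will not facilitate faster RTs or greater response frequency". That sentence does not say specificity will be judged by non-significance. Data analysis plans GEE with variable interactions, and both group and cued position are listed predictors, so a direct group-by-cue test is within the stated method.
- A reader might infer that the trial's localisation claim hangs on hypothesis 7. Research questions 1 and 2 are assigned to the spatial cueing task.

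**Conclusion.** The point holds for hypothesis 7. On the Schandry and water load tests its two predictions cannot both be tested and both succeed. Read as compatible, the own-test prediction is a ranking with about a 25% chance of appearing when the trained groups are equal and both beat control. Separately, predicting no significant difference is uninformative with about 20 per group: true differences of 0.2, 0.5 and 0.8 SD go undetected 91%, 66% and 31% of the time on one test, and 82%, 44% and 9% on both.

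These figures assume two-sided 0.05, independent tests, and standardised differences that the protocol does not supply. The textual conflict depends on none of them. The baseline comparison tests only chance imbalance. The consequence is limited to a secondary hypothesis; the primary reaction-time outcome is not affected.

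**What to change.** Restate hypothesis 7 in three parts.

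1. Remove the no-difference prediction for the Schandry task and the water load test, and remove the baseline comparison altogether.
2. State the own-test predictions as directional group-by-time contrasts: cardioception against gastroception, and against control, on the Schandry task; gastroception against cardioception, and against control, on the water load test. A crossed group-by-test contrast can be added as an optional overall test. At 0.5 SD on each test, with uncorrelated measures, its effect is (0.5 + 0.5)/√2 = 0.71 SD and its power at 20 per group is 0.59, against 0.338 × 0.338 = 0.11 for both separate tests being significant. It cannot replace the separate contrasts, because one test alone can drive it and it leaves out control.
3. For the MAIA and metacognitive awareness, report the difference in change between the trained groups with its 95% confidence interval, and claim similarity only if the interval lies inside a prespecified margin.

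The cost is rewording and a few contrasts within the planned GEE, with no new data. The drawback is that similarity will probably stay unproven. Since the half-width is about 0.64 SD at 20 per group, no smaller margin can ordinarily be met. Even the more lenient test by two one-sided 0.05 tests (80% power, true difference zero) needs about 2 × ((1.645 + 1.282)/m)² per group: 191, 69 and 27 for assumed margins m of 0.3, 0.5 and 0.8 SD. Because Trial status gives completion in August 2019, the restatement should be dated and marked as made before or after the group comparisons were seen.
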